### Effectiveness study

To determine the short- and long-term effectiveness of modified exercise and physical therapy on PAHCO and PA in persons undergoing rehabilitation, these effects will be compared with those of exercise and physical therapy conducted before modification (see Fig. 2). Owing to the prevailing organizational characteristics in the real-world setting, we will pursue a pragmatic evaluation approach based on a quasi-experimental design [46]. For this purpose, individuals undergoing inpatient medical rehabilitation will be recruited at two different time periods, namely, (a) prior to the development of modifications in the preparation phase, representing the control group (CG) receiving usual exercise and physical therapy, and (b) after the implementation of the modified exercise and physical therapy in the maintenance phase, representing the intervention group (IG) receiving modified exercise and physical therapy. In this context, we hypothesize that the changes in PAHCO and PA in persons undergoing rehabilitation after the modification of exercise and physical therapy (i.e., IG) will be significantly higher than the changes in PAHCO and PA in persons undergoing rehabilitation before the modification of exercise and physical therapy (i.e., CG).

#### Eligibility criteria

For inclusion in the study, the persons undergoing rehabilitation must fulfill the following eligibility criteria: (A) participation in an inpatient medical rehabilitation program at the respective time period (i.e., preparation phase for CG or maintenance phase for IG), (B) sufficient ability to read, comprehend, and write in the German language, and (C) provision of written informed consent to participate in the study. Accordingly, all participants who (A) discontinue the planned medical rehabilitation program, (B) have an insufficient ability to read, comprehend, and write in the German language, or (C) withdraw their original consent for participation are excluded.

#### Intervention

The participants in the CG will receive the usual exercise and physical therapy provided prior to the development and implementation of actions for modification. In Germany, a person undergoing rehabilitation usually receives approximately 11.8 h of physical and exercise therapy per week [47]. Exercise and physical therapy include services that use exercise and PA to achieve therapeutic goals (e.g., endurance, strength, and coordination training, treatments focusing on specific health conditions) that are organized either as individual or group sessions and delivered by qualified professionals (e.g., sports scientist, physiotherapists) [15]. The duration of the control period will correspond to the duration of the stay at the rehabilitation center, which is usually three weeks.

After the development and implementation of actions to modify exercise and physical therapy in the course of CP (see Study procedure), the participants in the IG will receive the modified exercise and physical therapy. Given the co-creation approach, the precise content of the modified exercise and physical therapy cannot yet be outlined in more detail. Similarly, the duration of intervention will equal the duration of the stay at the rehabilitation center (i.e., usually three weeks).

#### Outcomes

To evaluate whether the persons undergoing rehabilitation have acquired the competencies required to lead a healthy, physically active lifestyle, we will employ the PAHCO questionnaire with 42 items [48]. The assessment represents a self-report procedure and contains ten discriminant scales with theory-conform cross loadings across the three dimensions of movement competence, control competence, and self-regulation competence. The questionnaire has been validated in a stepwise manner across different target groups [14, 48]. Motivational competence for sport and exercise describes the self-determined ability to select convenient exercise and sport activities [49]. It has already been discussed as a motivational facet of PA-specific self-regulation competence within the original work on the PAHCO model [12], but an assessment instrument was only recently validated with a sample of adults [49]. Thus, we will complement the PAHCO assessment through the suggested scale with four items [49].

Among the secondary outcomes, we will operationalize the volume of PA by the two-dimensional “Bewegungs- und Sportaktivität” (BSA; Eng.: Physical Activity, Exercise, and Sport) questionnaire [50] which assesses leisure-time PA and sport activity over the past four weeks. The instrument specifies eight important activities of daily living (i.e., walking to work, walking to shopping, cycling to work, cycling for other reasons of transportation, taking a walk, gardening, strenuous housework, strenuous care work) for leisure-time PA and provides the opportunity to report three different, self-selected sport activities.

We will measure the general health status via the “Indikatoren des Reha-Status” (IRES; Eng.: Indicators of the Rehabilitation Status) questionnaire [51]. More specifically, we will use the IRES-24 questionnaire, which constitutes the short version of a comprehensive, 144 item self-report survey in the German language. The 24 items must be answered on either a five- or six-point Likert scale and encompass the sub-scales of subjective health, functionality in everyday life, physical health, and pain.

In addition, we will acquire basic sociodemographic data (e.g., age, sex, height, weight, employment status, and education), disease-specific information (e.g., indication/diagnosis, disease severity/degree of disability, comorbidities), and therapy-specific information (e.g., duration and content of exercise and physical therapy) of the persons undergoing rehabilitation. Primary and secondary outcomes are based on hypothesized intervention effects and are listed in Table 2.

**Table 2 Tab2:** Overview of data to be collected in the effectiveness study

Construct	Assessment and reference	Measurement time points		
		Beginning of medical rehabilitation (T0)	End of medical rehabilitation (T1)	1-year follow-up (T2)
**Primary outcome: Physical activity-related health competence (PAHCO)**				
Movement competence	PAHCO Questionnaire: subscales of movement competence [48]	X	X	X
Control competence	PAHCO Questionnaire: subscales of control competence [48]	X	X	X
Self-regulation competence	PAHCO Questionnaire: subscales of self-regulation competence [48]	X	X	X
	Questionnaire on motivational competence in exercise and sport [49]	X	X	X
**Secondary outcomes**				
Physical activity	“Bewegungs- und Sportaktivität” (BSA; Eng.: Physical Activity, Exercise, and Sport) questionnaire (with the dimensions leisure-time PA and sport activity) [50]	X		X
General health	Short version of the “Indikatoren des Reha-Status” (IRES; Eng.: Indicators of the Rehabilitation Status) questionnaire [51]	X	X	X
**Further participant data**				
Basic sociodemographic data	Questionnaire on age, height, weight, sex, work ability, employment status, education	X		
Disease-specific information^1^	Medical form stating indication/diagnosis, disease severity/degree of disability, comorbidities	X		
Therapy-specific information^1^	Documentation form stating duration and content of exercise and physical therapy		X	

Note: ^1^We cannot assume uniform assessments for these data, as the assessments may vary between the rehabilitation centers, for example due to different standard diagnostics or therapy documentation

#### Sample size

With the three PAHCO dimensions (i.e., movement competence, control competence, and self-regulation competence), the present study lists three main outcomes. We set *p* ≤.05 for the repeated multivariate analyses of covariance (MANCOVA) and assume a pre-post correlation (within-subjects factor) of *r* = .40, as a previous study revealed an autoregressive *r* = .418 [52]. To detect a significant intervention effect of medium magnitude (*η*^2^ = 0.04; *f* = 0.20) paired with a statistical power ≥ 80%, we must recruit a total of 244 persons undergoing rehabilitation. Given the number of rehabilitation centers (*n* = 3), we are advised to aim for 82 participants per center. Since each rehabilitation center includes persons undergoing rehabilitation at two time periods, that is, before modification (i.e., CG) and after modification (i.e., IG), we must recruit a number of *n* = 41 participants per time period in the respective rehabilitation center. Considering a longitudinal dropout rate of 15%, we aim to recruit *n* = 48 participants per time period in each rehabilitation center.

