#### Data analysis

The data set for persons undergoing rehabilitation will contain longitudinal data at the individual level. Specifiable as within-subjects factors, calculations can encompass comparisons between the beginning (T0) and the end of medical rehabilitation (T1) as short-term effects and respective comparisons with data at one year after starting medical rehabilitation (T2) as follow-up effects. In addition, the data set will contain longitudinal data on the level of the rehabilitation center (i.e., prior to the development of modifications, representing the CG, and after the implementation of the modified exercise and physical therapy, representing the IG; between-subjects factor). Since the effectiveness may vary among the three rehabilitation centers, we consider the setting as a control variate. We will integrate all these factors into repeated MANCOVA with the primary outcomes. To counteract outlier problems with the PA outcome, we will apply the winsorization technique to cut all values beyond the 95th percentile [53]. We will subsequently use the indicated frequencies and mean durations to calculate a corresponding total index in addition to a separate sport activity index. Calculations with the secondary outcomes will be treated as exploratory analyses. Nevertheless, we will adopt an intention-to-treat paradigm, meaning that all persons undergoing rehabilitation meeting the eligibility criteria and initially providing consent will be included in the statistical effectiveness computations. Reasonable dropouts (e.g., discontinuation of the planned medical rehabilitation program) will be treated as structurally missing data, whereas other missing items and measurements will be imputed with the expectation maximization algorithm [54]. We will run the analyses with the open source R (version 4.3.1 or higher) and interpret effect sizes (*η*²) according to the guidelines by Cohen [55], providing benchmarks to define small (*η*^2^ = 0.01), medium (*η*^2^ = 0.06), and large (*η*^2^ = 0.14) effects.

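### At f = 0.20, the 244 participants give 80% power for an F test with 2 numerator df; for the planned three-outcome MANCOVA, power on the natural reading is about 74–76% (3 df) or 62–64% (6 df)

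*Protocol article*

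**What the plan says.** The Sample size section of the effectiveness study takes the three PAHCO dimensions as primary: "the present study lists three main outcomes". It ties the error rate to the multivariate model ("We set *p* ≤.05 for the repeated multivariate analyses of covariance (MANCOVA")), and the authors "assume a pre-post correlation (within-subjects factor) of *r* = .40". The target is an "intervention effect of medium magnitude (*η*^2^ = 0.04; *f* = 0.20"), "paired with a statistical power ≥ 80"%. From these it concludes that "we must recruit a total of 244 persons undergoing rehabilitation". This becomes 41 per period per centre, raised to 48 for 15% dropout.

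The Data analysis section describes time (T0, T1, T2) as the within-subjects factor, control or intervention period as the between-subjects factor, and centre as a control variate. It then says: "We will integrate all these factors into repeated MANCOVA with the primary outcomes". It will interpret eta-squared on a published scale, "providing benchmarks to define small" (0.01), medium (0.06) and large (0.14) effects.

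Neither section gives the numerator df behind 244, the number of measurements or dependent variables entered, or what the effect size is defined on.

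**The concern.** The power statement is attached to a joint test of three outcomes, so a reader should be able to get from the listed inputs to 244 for such a test. The numerator df matter here: at a fixed effect and sample size, power falls as they rise. Two groups compared on change in three outcomes use 3 df over two time points and 6 df over three. If 244 was derived for a test with fewer df, the stated power belongs to another test. A null primary MANCOVA would then be read as coming from a study with at least 80% power at eta-squared 0.04 when the real figure may be lower.

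Separately, the planning effect is called medium in one section and lies below medium on the scale in another. A result exactly as planned would be reported as smaller than medium.

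**Working it through.** **Inputs (Sample size section).** Alpha 0.05; power 0.80; f = 0.20 or eta-squared = 0.04; r = .40; three outcomes; two groups. Three time points come from the Data collection section.

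**Effect conversion.** f² = eta²/(1 − eta²). Eta-squared 0.04 gives f = √(0.04/0.96) = 0.204; f = 0.20 gives eta-squared = 0.04/1.04 = 0.0385. The gap is ordinary rounding. Both values are carried below.

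**Formula.** For two groups the multivariate group × time test is an exact F test with df1 = (number of outcomes) × (number of time points − 1), df2 = N − 1 − df1 and noncentrality λ = N·f². Power is the probability that the noncentral F exceeds the central 95% point. Reducing df2 for centre changes power by less than 0.1 percentage point.

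**The plan's own figure.** At N = 244 and f = 0.20, λ = 244 × 0.04 = 9.76. With df1 = 2, df2 = 241, the critical value is 3.03 and power is 80.02%; N = 243 gives 79.8%. So 244 is exactly the smallest N for 2 df. With two groups that is one outcome over three time points; three groups at two time points also gives 2 df and 244. Neither uses r.

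**With r = .40 entered.** The usual within-between formula has λ = f²·N·m/(1 − r), where m is the number of time points. For two time points N = 61 (λ = 0.04 × 61 × 2/0.6 = 8.13); for three, N = 50 (λ = 10.0). A one-outcome change-score test, λ = N·f²/[2(1 − r)], needs 238. That is near 244, but it is still a single-outcome test.

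**The planned three-outcome test, with the stated effect taken as that of the joint test:**

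| df1 | Meaning | Power at 244 (f = 0.20 / eta² = 0.04) | N for 80% (f = 0.20 / eta² = 0.04) | Eta² detectable with 80% at 244 |
|---|---|---|---|---|
| 2 | see above | 80.0% / 81.7% | 244 / 235 | 0.038 |
| 3 | three outcomes, T0–T1 | 74.2% / 76.1% | 277 / 266 | 0.043 |
| 6 | three outcomes, T0/T1/T2 | 61.8% / 63.9% | 347 / 334 | 0.054 |

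**At the plan's own medium.** Eta-squared 0.06 gives f = 0.253 and λ = 15.57. N = 244 then gives 92% (3 df) and 85% (6 df).

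**Dropout step.** 41/0.85 = 48.2, taken as 48; 48 × 6 = 288; 288 × 0.85 = 244.8. This chain is consistent. If all 288 were analysed, power would be 82–83% (3 df) and 71–73% (6 df).

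**Sensitivity to the effect definition, N = 244.**
- f on the raw scale with baseline-adjusted variance: λ = 9.76/(1 − 0.16) = 11.62, power 82% (3 df) and 71% (6 df).
- f on the raw scale with change-score variance: λ = 9.76/1.2 = 8.13, power 65% and 53%.
- f = 0.20 in each outcome separately: 3-df power depends on the correlation between outcomes, which is not given. Assuming 0 to 0.9, it runs from 99.8% down to 77%.

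**The case against.** Four arguments limit the point.

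1. The document does not say what f is defined on. Under some definitions 3-df power reaches or exceeds 80%; under others it is worse than in the table. This stands: 62–76% is conditional.
2. The Data analysis section describes T0 against T1 as the short-term effect and comparisons with T2 as follow-up effects. Those can be read as two-time-point contrasts with 3 df each. The sentence integrating all factors permits a 6-df omnibus test but does not fix it. This also stands, so the lower end should not be presented as the planned test.
3. The 244 is what remains after 15% longitudinal loss. T0–T1 spans a stay of usually three weeks, whereas T2 is a postal survey at one year. If most loss comes late (an assumption), the short-term analysis has nearly 288 people and about 82–83% power. This stands for T0–T1 only. Imputation does not restore the information lost by T2.
4. A condensed article may leave software settings to a fuller document. That excuses missing detail. It does not make the listed inputs lead to 244 for the test named: no three-outcome variant tried at alpha 0.05 and 80% power returned it.

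A reader might go further and infer that the trial is underpowered, or that the authors must have powered a single outcome over three time points. The documents support neither. At eta-squared 0.06 the sample is ample, and more than one 2-df design yields 244.

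**Conclusion.** The point holds in limited form. The article attaches 244 and at least 80% power to a three-outcome repeated MANCOVA, but at f = 0.20 the number is the 2-df answer, and r = .40, listed as an input, does not produce it.

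If the stated effect is that of the joint test and 244 people are analysable, the shortfall against 80% is about 4–6 percentage points for T0–T1. It is about 16–18 points if a single test over all three time points is meant. In terms of effect size, the detectable eta-squared moves from the stated 0.04 to 0.043 or 0.054.

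The conflict between 0.04 and 0.06 as medium needs no assumption; it is a plain inconsistency between two sections.

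This should be corrected, but it does not call the recruitment target into question.

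**What to change.** Leave 48 per period per centre as it is and revise the text.

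- State the test, the numerator df and the effect definition to which 244 refers, and say whether the primary test is the T0–T1 comparison or one test over T0, T1 and T2.
- Restate the figure, for example: with 244 analysable participants, power is 80% for a multivariate group × time eta-squared of 0.043 (T0–T1, 3 df) or 0.054 (T0/T1/T2, 6 df). Alternatively, keep 0.04 and give power as about 74–76% or 62–64%.
- Stop calling 0.04 medium, or plan on the 0.06 of the Data analysis section, for which 244 gives 92% (3 df) and 85% (6 df).
- Remove r = .40, or show where it enters.

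The cost is wording only, with no extra participants. The downside is that the stated power or detectable effect becomes slightly less favourable.

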Although the present study may add value to PAP within medical rehabilitation, we consider the following limitations. First, all rehabilitation centers are longitudinally compared against their previous concept (i.e., intra-organizational control with intervention and control periods). Against this background, we cannot fully exclude that cohort or historical effects over time (e.g., reforms of the entire rehabilitation system, severe disease waves, labor disputes of therapist associations) may affect the results, which cannot be methodologically controlled by this study design. In any case, we will closely follow relevant processes within the rehabilitation centers (e.g., other interventions being conducted in parallel with our study) as well as the political atmosphere, health-related debates, and upcoming guidelines relevant for the German rehabilitation system (e.g., via the expert panel) to provide potential explanations for the final interpretation of the results. Furthermore, the study procedure causes a 16-month time gap between the measurement time points of the CG and the IG, so that potential seasonal effects cannot be eliminated. However, the seasonal effects across the three rehabilitation centers are not systematically distributed for either the IG or the CG because of the sequential design and the associated measurement time points. Second, to the best of our knowledge, this study is the first to apply a co-creation approach to modify exercise and physical therapy in medical rehabilitation, with the aim of promoting long-term PA among persons undergoing rehabilitation in Germany. Owing to the complex approach to modifying the therapy concept, the study can only include three rehabilitation centers. Accordingly, we can only treat the rehabilitation centers as covariates instead of systematically considering the cluster effect through multilevel modeling (for sample requirements, see [58]).

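### The 244 participants give at least 80% power only if change scores are uncorrelated within the six centre-period cells, and the centre covariate does not secure that

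*Protocol article*

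**What the plan says.** The Sample size section sets alpha at 0.05 "for the repeated multivariate analyses of covariance (MANCOVA"), takes η² = 0.04 (f = 0.20), asks for "statistical power ≥ 80"%, and concludes "we must recruit a total of 244 persons undergoing rehabilitation". The total is then divided: "we are advised to aim for 82 participants per center", and 41 per recruitment period within each centre, raised to 48 for 15% dropout. The only correlation named is the one within a person over time (r = 0.40). None is given between patients.

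The introduction to the Effectiveness study defines CG and IG by recruitment period within each centre: CG before the modification, IG after it. The Intervention section describes therapy as "organized either as individual or group sessions and delivered by qualified professionals". The Data analysis section enters the centre into the repeated MANCOVA as a control variable. The Discussion gives the reason for going no further: with three centres, "we can only treat the rehabilitation centers as covariates instead of systematically considering the cluster effect through multilevel modeling". It also says that historical effects over time cannot be controlled by this design.

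**The concern.** Treatment is assigned to whole centre-periods, not to patients. Patients in one cell share the season, the staffing of that period, the local version of the therapy and, in part, the therapy groups. If any of this makes their changes more alike than those of patients in another cell, the IG–CG contrast is less precise than the number of patients suggests.

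A centre covariate does not cure this. It removes a centre's level to the extent that both periods share it. A deviation specific to one centre in one period falls on one side of the IG–CG comparison and stays in it.

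At stake are the precision and the error rate of the primary comparison: power below the stated figure, and p-values that are too small. The article says that the findings will determine dissemination in the German rehabilitation sector, so intervals that are too narrow would matter. The Discussion's limitation does not reach the Sample size section, where the power carries no condition, or the Data analysis section, where the tests carry none.

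**Working it through.** **Inputs from the Sample size section.** Alpha 0.05, f = 0.20 (f² = 0.04), power at least 80%, N = 244, 3 centres × 2 periods, m = 41 per cell (6 × 41 = 246).

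**Assumed, because the documents do not give it.** ρ, the correlation of change scores between patients of the same centre-period: 0.005, 0.01, 0.02, 0.05.

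**Step 1. Reproduce 244.** Take independent patients, two groups and three time points, so the group-by-time test has 2 numerator df. The noncentrality is λ = N·f² with N − 3 denominator df.
- N = 243: λ = 9.72, power 0.7984.
- N = 244: λ = 9.76, power 0.8002.

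So 244 is the smallest N that reaches 80% when patients are independent. The article does not state the df. With 1 df the answer would be 199 and with 3 df 277, so the 2-df calculation is inferred from the match. The dropout allowance adds no slack: 6 × 48 = 288 and 288 × 0.85 = 244.8.

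**Step 2. Variance of the contrast with centre as a covariate.** The estimate is the mean over three centres of (IG cell mean − CG cell mean). If σ² is the variance of a change score, a cell mean has variance (σ²/m)·[1 + (m − 1)ρ]. The contrast therefore has variance

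(1/9) × 3 × 2 × (σ²/m)·[1 + (m − 1)ρ] = (2σ²/3m)·[1 + (m − 1)ρ].

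The design effect is DE = 1 + 40ρ, even though centre is in the model.

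**Step 3. Power and error rate.** Power is from noncentral F(2, 241) with λ = 9.76/DE. The true error rate of a nominal 5% single-df contrast is 2 × [1 − Φ(1.96/√DE)].

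| ρ (assumed) | DE | 244/DE | λ | Power, 2 df | True error rate, 1 df |
|---|---|---|---|---|---|
| 0 | 1.0 | 244 | 9.76 | 80% | 5% |
| 0.005 | 1.2 | 203 | 8.13 | 72% | 7% |
| 0.01 | 1.4 | 174 | 6.97 | 65% | 10% |
| 0.02 | 1.8 | 136 | 5.42 | 53% | 14% |
| 0.05 | 3.0 | 81 | 3.25 | 34% | 26% |

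The last two columns refer to different tests: the 2-df test that reproduces 244, and a single-df IG–CG contrast. A single-df contrast at N = 244 starts from 87.5% power and falls to about 81, 75, 64 and 44% over the same ρ values (with m = 244/6 = 40.7).

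**Step 4. Would more patients help?** With six cells, 244/DE generalises to 6m/[1 + (m − 1)ρ], which cannot exceed 6/ρ. To reach 244, m must be 244(1 − ρ)/(6 − 244ρ). That is about 305 patients in total at ρ = 0.005, 407 at 0.01 and 1,281 at 0.02. From ρ = 6/244 ≈ 0.025 upwards it cannot be reached.

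**Step 5. Would standard errors clustered by admission week help?** I simulated 246 patients in six cells of 41, spread over an assumed 17 weeks (about 2.4 patients per week), with centre as a fixed effect.
- Correlation at centre-period level, ρ = 0.01/0.02/0.05: error rate about 10/14/26% with ordinary standard errors and about 10/15/25–26% with week-clustered ones. Nothing is corrected.
- Correlation only within admission weeks: DE = 1 + 1.41ρ, so 1.01 to 1.07 for ρ = 0.005 to 0.05, and power 80 to 77%. There is little to correct.

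**The case against.** Four arguments on the other side deserve an answer.

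*The limitation is disclosed.* The Discussion says openly that the cluster effect is not modelled, that three centres are too few for multilevel modelling, and that historical effects cannot be controlled. This stands as disclosure, and the reason given against random centre effects is sound. A reader might infer that the sponsor overlooked clustering, and the text does not support that. What is missing is the consequence: the power and the tests are stated as if the limitation did not exist.

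*The relevant correlation may be small.* The hypothesis concerns changes, so case mix that is stable over time cancels, and the 1-year measurement is a postal questionnaire long after discharge. The article does not say what share of therapy is given in groups, or whether staff differ between periods. This stands. It is why ρ must be defined for change scores and shown as a range. A reader might take one row of the table, such as 65% power, as the trial's true power. Nothing in the documents supports choosing a row.

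*Variance estimation belongs in the analysis plan.* As a general rule it does. Here, however, the article itself fixes the basis of the power and says how centres will be handled, so the point concerns what is stated.

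*No ready analysis removes the problem.* This also stands. A reader might look to standard errors clustered by admission week, on the view that many small intake cohorts supply enough clusters. Step 5 shows that this leaves centre-period correlation untouched and would give false reassurance. The number of weeks is also unsupported for the IG: the four months are stated for the preparation phase, and the length of IG recruitment in the maintenance phase is not given.

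**Conclusion.** The point holds as one about conditional power and conditional p-values. The 244 is exactly an independent-patient figure under the 2-df calculation that reproduces it, so any positive correlation of change scores within centre-periods takes that test below 80% power. It also takes the error rate of a nominal 5% IG–CG contrast above 5%. The direction is certain. The size rests on an assumed ρ: over 0.005 to 0.05, power of about 72 to 34% and an error rate of about 7 to 26%.

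Two stronger conclusions do not follow. The documents do not show that the trial is underpowered by a known amount, because they give no ρ. Nor do they show that more patients should be recruited: with six cells, extra patients help only while ρ is well below 0.025.

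**What to change.** - **Sample size:** state that at least 80% power at 244 assumes no correlation of change scores within centre-periods, and give the power over ρ = 0.005 to 0.05, marked as assumed values.
- **Data analysis:** add a sensitivity result in which the variance of the IG–CG contrast is multiplied by 1 + (m − 1)ρ over the same range, with m the achieved cell size. Report the three centre-specific IG–CG differences beside the pooled one, so that readers can see whether they agree.
- **Discussion:** state that centre covariates do not remove correlation specific to a centre-period, so the p-values are conditional on these three centres and these periods.
- Do not offer standard errors clustered by admission week as the remedy.

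The cost is a few sentences and a short calculation on results that will exist anyway. The sensitivity intervals will be wider and the stated power less favourable. No extra patients, data or design changes are needed.
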